### 4.4.8 Sample size

Using the formula for cluster randomised trials suggested by Hayes and Bennett ([Hayes and Bennett 1999](#_ENREF_36)),

**n = D(Z_α/2_ + Z_β_)^2^[π_0_(1- π_0_) + π_1_(1- π_1_)]/ (π_0 +_  π_1_)^2^** where

- **n** = number of participants in each arm,
- **D** = the design effect of 2.5,
- **Z_α/2_** = 1.96,
- **Z_β_ = 0.84,**
- **π_0_ =** current rate of institutional deliveries, 23.5%
- **π_1_** = estimated rate of institutional deliveries after the intervention, 33.5%

Substituting in the formula, we obtain a sample size of 788; allowing for a 10% loss-to-follow up we estimate a total population of 868 participants per arm. Further substituting in the formula for required number of cluster, C

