**C=1+(Z_α/2_ + Z_β_)^2^[π_0_(1- π_0_)/n + π_1_(1- π_1_)/n + k^2^(π_0_^2^ _+_ π_1_^2^)]/ (π_0 +_ π_1_)^2^**

Substituting for n=868, we arrive at a cluster number of 8 per arm; two arms will therefore require 1,736 participants distributed between 16 health centres; implying an average of 108 pregnant women enrolled per health centre for the entire four months. This will necessitate recruiting an average of 27 pregnant women per health centre per month.

This sample is based on the following assumptions:

- A degree of error, 0.05
- (95% confidence interval, **Z_a_** =1.96),
- the power to detect a significant difference between two comparison groups of 80% (**Z_a/2_** =0.84) to detect a 10% difference;
- **π_0_**, the current prevalence of institutional deliveries 23.5% ([DHO 2010](#_ENREF_28));
- **π_1_**, expected prevalence of institutional deliveries after the intervention 33.5% and
- A design effect **D,** 2.5 and
- Coefficient of variation between clusters of the same group **k_m_,** 0.25

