**A: Socio-demographic characteristics**

1. Code number..........................................................................................
2. Name of household Head........................................................................
3. Age of Respondent in completed years (lactating woman)....................
4. Parity of respondent 1, 2, 3, 4, 5, over 5
5. Highest education level attained:
6. Non
7. Primary;
8. Secondary;
9. High school;
10. Tertiary;
11. Marital status:
12. Married
13. Single
14. Separated
15. Divorced
16. Widowed
17. What do you do for a living:
18. Nothing
19. Housewife
20. Farming/gardening
21. Selling in the market/petty trade
22. Business woman
23. Salaried
24. Did you attend any ANC during the last pregnancy:
25. Yes, 2. No
26. Number of ANC visits made with the last pregnancy:
27. 0,
28. 1,
29. 2,
30. 3,
31. 4
32. More than 4
33. Where did this last delivery take place:

**1)** Home;

**2)** Health facility;

**3)** On the way to health Facility

1. How old is the baby now? Age in completed weeks
2. 0-1 week **2)** 2-4 weeks **3)** 5-8 weeks **4)** 9-13 weeks
3. Number of living children: 1, 2, 3, 4, 5, 6, more than 6
4. Number of deceased children: 0,1, 2, 3, 4, 5, 6, more than 6

(*if deceased babies is* ***0*** *then skip to section* ***B***)

1. At what ages did the deceased children die?

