**H. Care seeking**

Newborn immunisation

1. Is the newborn already immunised for

1. Polio zero 1=Yes 2=No
2. BCG 1=Yes 2=No
3. Polio 1 1=Yes 2=No
4. DPT HEB+Hib (pentavalent) 1=Yes 2=No

2.Did this newborn fall ill in the last three months? 1=Yes 2=No)

(*if NO conclude the interview*)

3. If yes how did you detect the illness? *(Circle all that apply)*

1. Failure to feed
2. Excessive crying
3. Less activity
4. Warm to touch

4.What immediate actions did you take? *(Circle all that apply)*

1. Attention to VHT
2. To Health centre
3. Seek medication at home
4. Traditional healers
5. Went to private clinic
6. Did nothing

5.How soon after the onset of illness did you seek for care?

1. Within one hour
2. Within six hours
3. Within 24 hours
4. After 24 hours
5. What in your view was the cause of illness?
6. Evil spirit
7. Some evil neighbours or relatives
8. Bad air
9. The infected umbilical stump
10. Acquired from place of delivery
11. Acquired from mother
12. No idea

Thank you for your time

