# Annex 15: SOPs: Standard Operating Procedure and intervention packages

### i) Standard operating procedure and intervention package for educational intervention during ANC

**(**[**Bhutta Z, Sajid S et al. 2011**](#_ENREF_10)**)**

When the pregnant women enter the clinic room

1. Identify pregnant women with all of the following conditions:
2. First visit of the current pregnancy,
3. Not more than 28 weeks of gestation
4. Administer the consent form
5. If she consents then open a file for her
6. Request for her ANC card
7. Enter all personal details available on the ANC card in to the file
8. Record any telephone contacts that you can use to access her in future

name, age, ethnicity, parity, LNMP, EDD, gestation age of the first visit, history of previous pregnancy outcome of the previous pregnancy (baby – alive or dead, mode of delivery), distance from the health facility, marital status, history of previous ANC attendance-Number of attendance, delivery (home, health facility, TBA etc).

Note the date for the next appointment, (all this information will be used to tailor the discussions)

-if she consistently attended all the expected milestones-then you find out what her motivation was to do so, and whether she plans to do the same for the current pregnancy;

- If not consistent-discuss the reasons for inconsistencies and help her to find a solution,

- diet during pregnancy-find out what foods are readily consumed and what she can easily afford, what foods could be prohibited during pregnancy (caution about antagonising cultures-you can find another acceptable alternative source of the food value) and discuss the importance for balances in diet, fruits, green vegetables, proteins and carbohydrates,

- Discuss work related activities-how much she does and who helps her with the routine household and garden chores.

- Discuss importance of ANC even when she has been attending consistently, the advantages of delivering in the health facility even when she has been delivering at the health facility,

- Birth preparation-clean clothes for the newborn (emphasis that clean does not mean new!-even old rages can be patched together washed clean, clean environment for the newborn,

- caring for the cord, dangers of applying substances to the cord,

- Pre-lacteal feeds-and its disadvantages-explain how breast milk eventually comes and the usefulness of colostrum.

- Discuss bathing of the new baby how soon and how to delay (delay up to 24 hours),

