- Immunisation of the child, polio 0, BCG etc.

- Recognition of a sick child-hot to touch, refusing to feed, crying unusually,

All these information should be derived from discussions with the pregnant woman-not as a set of instructions to be strictly followed-compromises should be made at every stage-all that is agreed upon should be detailed down in the file. The counsellor should moderate the discussions, if the pregnant woman has come with a partner or a caretaker; both of them should be involved in the discussions even if the care taker is not pregnant-if there is a caretaker present then this should be recorded and state the relationship between them.

Tick the areas that were discussed, mark with a cross what you did not discuss with her, note down important decisions that you have agreed upon with the participant-you will use this as a reference point in subsequent meetings and discussions

Ensure that the discussion does not exceed 30 minutes unless there is expressed interest from the participant to continue. And this expression should be noted down in the file.

For subsequent visits indicate appointment dates and actual revisit dates

Later on follow-up for delivery and record where she has delivered from

Assess for the different practices outlined annex 6 will be used to assess the following outcomes

Place of delivery, Cutting of the cord, care for the cord, initiation of breast feeding, provision of pre-lacteal feeds, in case of illness how it was recognised, what action was taken, how soon was the care seeking from onset of disease or when the decision was made that the child was unwell, what facility did she take the child, outcome, at the periphery of assessment the researcher will want to know whether the child is still alive just at one month.

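### Place of delivery, the outcome that sets the sample size, rests on the mother's unverified answer while only one arm is individually counselled on facility delivery, so over-reporting that differs by arm could mimic an effect

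*Protocol*

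**What the plan says.** Institutional delivery is one of several primary outcomes (Protocol 4.4.1, 4.4.7) and the only one used for the sample size (4.4.8). The operational definitions count birth in any health centre II, III or IV or hospital.

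Annex 15 i) instructs staff: "Later on follow-up for delivery and record where she has delivered from". That sentence names no source. The next one does: it makes Annex 6 the tool for a list of outcomes that begins with place of delivery. Annex 6 is a structured interview of the lactating woman.

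- Section A asks "Where did this last delivery take place", with three options (home, health facility, on the way).
- Section C asks for place again with five options, and for mode of delivery and attendant.
- Section H asks "Is the newborn already immunised for" and takes yes or no for Polio 0, BCG, Polio 1 and the pentavalent vaccine.

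No item asks which facility, and none asks to see a document. The baby's age is recorded only in bands of weeks. A check against a maternity register, discharge slip or child health card appears nowhere in the protocol.

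The intervention script includes "the advantages of delivering in the health facility even when she has been delivering at the health facility" and newborn immunisation. What is agreed goes into the woman's file for use at later meetings. Reminders, passed on by community health workers, cover return visits and delivery due dates (4.4.5, Annex 15 ii). Annex 9 describes the control arm as having no individualised education, no community health workers and no phones. The limitations in 5.1 do not mention reporting bias.

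**The concern.** In the intervention arm a woman discusses facility delivery individually, has her decisions written down, is reminded of her due date, and is then asked whether she delivered in a facility. A control woman has no comparable individual exchange. If some women who delivered elsewhere give the answer they think is hoped for, this may well happen more often in the intervention arm, and the excess would be counted as effect. An independent or masked interviewer would not remove it, because the error lies in the respondent's answer. At stake is the outcome on which the trial is powered, although that outcome is an event that usually leaves a record.

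**Working it through.** **Inputs, all from Protocol 4.4.8**

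- "current rate of institutional deliveries, 23.5" per cent and "estimated rate of institutional deliveries after the intervention, 33.5" per cent, a difference of 10 points
- "A degree of error, 0.05" with Z = 1.96, and 80% power with Z = 0.84
- Design effect 2.5
- 788 women per arm, or 868 after allowing 10% for loss

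**The plan's own figure.** With the squared difference of the two rates in the denominator (the printed formula shows their sum, which would give only 24):

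2.5 × (1.96 + 0.84)² × [0.235 × 0.765 + 0.335 × 0.665] / 0.10² = 2.5 × 7.84 × 0.40255 / 0.01 = 789, against 788 stated.

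788 × 1.10 = 866.8, against 868 stated. The inputs are therefore understood as the protocol used them.

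**Apparent effect with no true effect.** Let both arms have a true facility-delivery rate of 23.5%, so that 76.5% deliver elsewhere. Let a share s of those women in the intervention arm, and a share c in the control arm, report a facility birth that did not happen. Reported rates are 0.235 + 0.765 s and 0.235 + 0.765 c, and the apparent difference is 0.765 × (s − c). Only the excess s − c matters for its size. The documents give no value for s or c, so the range below is assumed. The chance of a significant result is for a two-proportion test with effective size n/2.5 and c = 0.

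| Excess s − c | Apparent difference (points) | Chance of p < 0.05, n = 788 to 868 |
|---|---|---|
| 3% | 2.3 | about 10% |
| 5% | 3.8 | 20–21% |
| 10% | 7.7 | 58–62% |
| 13.1% | 10.0 | 80–83% |
| 20% | 15.3 | 99% |

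The 13.1% row is solved backwards from the planned effect: 0.10 / 0.765 = 0.131. It corresponds to 0.10 × 788 ≈ 79 women, or 0.10 × 868 ≈ 87, in the intervention arm.

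**Smallest excess that would reach significance.** With the design effect, the smallest significant difference is 6.9 points (n = 788) or 6.6 points (n = 868). Dividing by 0.765 gives an excess of 9.1% or 8.6%, about 55 to 57 women. With a plain chi-square that ignores clustering, the thresholds are 4.3 or 4.1 points, an excess of 5.6% or 5.4%. Section 4.4.10 names the chi-square test followed by logistic regression and states no allowance for clustering.

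**Immunisation.** The protocol gives no baseline rate, so no figure is computed.

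**The case against.** - **The documents do not say that women will misreport.** This stands. Place of birth, asked within about four weeks of the end of pregnancy (4.4.6), is a recent and memorable event, and every over-reporting rate above is assumed.
- **A reader might infer that false reports arise in the intervention arm only and always favour it.** The documents do not support that. Control women also attend antenatal care and sometimes receive group health education (4.4.5), and the counselling training in 4.4.6 is not limited to one arm. They may over-report too, so only the excess counts.
- **A reader might picture women repeatedly told for 30 minutes what is expected of them.** Annex 15 i) makes 30 minutes a normal ceiling and frames the session as discussion with compromise, not instruction. The listed reminders do not include immunisation.
- **Self-report of immunisation is inferred.** This stands. The outcome list in Annex 15 i) omits it; Annex 6 section H asks about it and no other source is given. Annex 6 is also headed as the tool for sub study two, and 4.4.9 speaks only of semi-structured questionnaires. For place of delivery, however, Annex 15 i) names Annex 6 outright, so the source is fixed in the protocol and not left to an analysis plan.
- **Annex 6 has an internal check.** Place is asked twice, along with mode and attendant. This helps a little, but all the answers come from the same respondent.
- **Records can mislead as well.** This stands. Births may occur in any of 42 health centres or the hospitals (4.1), not only the 16 trial centres, and record completeness or tracing could differ by arm. A definition based on records alone is therefore not clearly better.

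**Conclusion.** The concern holds in a limited form. The outcome that determines the sample size is taken from the mother's answer with no stated verification, in a trial with visibly different arms where only one arm receives individual discussion and reminders about facility delivery. Immunisation appears to share the weakness. With no true effect, an excess of over-reporting of 5% among women without a facility birth would give 3.8 points, 10% would give 7.7, and 13.1% would give the whole planned 10 points. This rests on a true rate of 23.5% in both arms and on assumed excess rates. It shows that such bias could produce the effect, not that it will. The open character of the trial is inferred from the design and from the absence of any stated masking.

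**What to change.** 1. Add the name of the facility and the date of birth to the delivery item in Annex 6.
2. At the interview already planned, and in the same way in both arms, ask to see the discharge slip or child health card. Record whether place of delivery, Polio and BCG were confirmed by document or rest on report only.
3. Where feasible, check the maternity register of the named facility.
4. State in 4.4.7 and 4.4.10 that institutional delivery and immunisation will be given both as reported and as record-confirmed, with agreement between report and record shown by arm. State also that a facility-delivery effect not seen in the record-confirmed result will be treated as possible reporting bias.
5. Name Annex 6, or another source, explicitly for immunisation in Annex 15 i), and add reporting bias to 5.1.

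The cost is two form fields, a slightly longer interview and some register visits, which may extend beyond the 16 trial centres. Some true facility births will have no record, possibly not equally in the two arms, which is why the record-confirmed result should stand beside the mother's report and not replace it.

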### 4.4.9 Sampling procedure

Sixteen health centres in total will be proportionally selected from both Masindi and Kiryandongo district with Masindi contributing to 10 and Kiryandongo contributing to 6 HCs. A community trail involving two arms will be tried.

*Selection of the experimental units (pregnant women)*

Ten and six health centres will be proportionally selected from Masindi and Kiryandongo district giving a total of 16 heath centres in the trail.

From the 16 selected health centres, 8 of these will be purposively assigned to each of the two arms to minimize contamination. In each of the 8 health centres on each trial arm, 868 pregnant women with 28 weeks of pregnancy or below will be enrolled as they come in giving a total of 1736 in this trial. Health centres on two extremes of the districts will be assigned to either the intervention or the control group in order to avoid contamination between the two.

*Data Collection tools and procedures*

Semi-structured questionnaires written in English but administered in Runyoro will be used by research assistants.

*Training of research assistants*

Data collectors will be recruited and trained on data collection methods for two days. Training will include how to conduct individual interviews and data collection skills

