## Annex 9: Sub study three Flow-diagram for educational intervention

**Arm 1**

Routine ANC & Newborn Services only

Absence of individualised prenatal health education; no CHW deployed; no mobile phones

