### iii) Standard Operating Procedure for Health Assistants based at the health facility

1. Health assistant will draw a timetable for all three CHWs who will provide regular prenatal education interventions at the health facility
2. He/she will make routine fortnightly field visits to the CHWs providing services at the primary care facility
3. He/she will organise monthly face-to-face sessions with CHWs providing educational interventions at the health facility
4. He/she will ensure that the forth ANC first attendant is appropriately sampled
5. Ensures that all details regarding the prenatal woman is accurately entered and archived by the CHWs

Ensures recordings of the monthly sessions with CHWs are recorded and archived to be shared with the PI during the bi-monthly field visits

**Annex 15:** HOUSEHOLD EMPOWERMENT-‘ENABLEMENT’

The Patient-Enabling-Initiative PEI tool, adapted from ([Howie J, Heaney D et al. 1998](#_ENREF_42)), will be used to assess secondary outcome measures ([Lewin S, Munabi-Babigumira S et al. 2010](#_ENREF_54)): This tool will be administered to those women who have attended the intervention arm

Household Empowerment tool

|  | **As a result of your interaction with the VHT did you feel you** | **Much better** | **better** | **Same or less** |
| --- | --- | --- | --- | --- |
| 1 | Are able to **cope** with your routines during pregnancy, delivery and caring for newborn care? |  |  |  |
| 2 | Are able to **understand** what is going on during pregnancy, labour and your newborn during the next pregnancy? |  |  |  |
| 3 | Were you able to **cope** with the pregnancy, delivery and care for the newborn? |  |  |  |
| 4 | Were **able** to keep yourself and the newborn healthy? |  |  |  |
|  |  | **Much more** | **more** | **Same or less** |
| 5 | Were **confident** about your health and the health of the newborn? |  |  |  |
| 6 | Were able to take care of yourself and the newborn? |  |  |  |

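### The protocol gives two unreconciled accounts of who ascertains the primary outcomes; under one of them, the unblinded intervention team records them in the intervention arm only

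*Protocol*

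**What the plan says.** The primary outcomes of sub study three are timely return visits, four completed antenatal (ANC) visits, institutional delivery and newborn homecare practices (4.4.1).

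**Account A, main text and budget.** Section 4.4.9 says: "Semi-structured questionnaires written in English but administered in Runyoro will be used by research assistants". The data collectors are recruited for the purpose and trained for two days. Section 4.4.10 has the principal investigator check completed questionnaires and supervise collection. The budget has an assessment phase that pays 12 research assistants for 10 days. None of this distinguishes the arms.

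**Account B, Annex 15.** Part i) is the procedure and package for the educational intervention. It runs from eligibility and consent ("If she consents then open a file for her") through counselling to outcome data:
- Visits: "For subsequent visits indicate appointment dates and actual revisit dates".
- Delivery: "Later on follow-up for delivery and record where she has delivered from".
- Newborn practices: "Assess for the different practices outlined annex 6 will be used to assess the following outcomes".

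Part iii), for the Health Assistant, adds: "Ensures that all details regarding the prenatal woman is accurately entered and archived by the CHWs".

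The promotional team of one Health Assistant and three CHWs belongs to the intervention arm (4.4.5, Annex 9). Annex 9 describes the control arm as: "Absence of individualised prenatal health education; no CHW deployed; no mobile phones". The protocol contains no recording procedure for control centres and no statement about masking outcome assessors.

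**The concern.** A reader who implements the protocol cannot tell which account governs. Under Account A, one group of interviewers covers both arms. Under Account B, the people who advise a woman to deliver in a facility later record whether she did, and control-arm data have to come from somewhere else.

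Account B matters because place of delivery and newborn practices, if taken from the mother, are self-reported. A woman may give her counsellor the answer she thinks is wanted, and the counsellor knows the arm and the aim. If that happens in one arm only, the error favours the intervention, and nothing collected under the plan would let the analysis separate it from a true effect. Return visits and visit counts are less exposed, because 4.4.6 has qualified staff record ANC details on the woman's card.

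**Working it through.** **Step 1. The two accounts by outcome.**

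| Outcome | Account A (4.4.9, 4.4.10, budget) | Account B (Annex 15) | Exposure to reporting bias |
|---|---|---|---|
| Timely return, four visits | Research assistants | Dates entered in the file opened at the education session | Lower: ANC card exists |
| Place of delivery | Research assistants | Followed up and recorded under the education procedure; no actor named | Higher if self-reported |
| Newborn practices | Research assistants | Annex 6 tool; no actor named | Higher: interview with the mother |

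Annex 15 therefore touches all four primary outcomes. It names CHWs explicitly only for entering and archiving details of the prenatal woman.

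**Step 2. Reproduce the plan's sample size, to anchor the illustration.** Inputs from 4.4.8: p0 = 0.235, p1 = 0.335, D = 2.5, z-values 1.96 and 0.84. The denominator must be read with a minus sign; the printed plus sign gives about 24.

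n = 2.5 × (2.80)² × [0.235 × 0.765 + 0.335 × 0.665] / (0.10)² = 2.5 × 7.84 × 0.40255 / 0.01 = 789.0

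The protocol states 788, which agrees to within rounding. With 10% added it becomes 868 per arm.

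**Step 3. What misrecording under Account B could do.** Assume that the true facility rate is 23.5% in both arms, that 788 women per arm are analysed, that the test respects D = 2.5, and that a fraction r of non-facility births in the intervention arm is recorded as facility births. The documents give no value for r, so a range is shown.

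- Spurious difference: b = (1 − 0.235) × r = 0.765 r
- Recorded intervention rate: q = 0.235 + b
- SE = √{2.5 × [0.235 × 0.765 + q(1 − q)] / 788}
- P(significant) = Φ(b/SE − 1.96) + Φ(−b/SE − 1.96)

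| r (assumed) | q | b (points) | SE | b/SE | P(significant) |
|---|---|---|---|---|---|
| 0 | 0.2350 | 0 | 0.0338 | 0 | 5% |
| 2% | 0.2503 | 1.5 | 0.0341 | 0.45 | 7% |
| 5% | 0.2733 | 3.8 | 0.0346 | 1.10 | 20% |
| 10% | 0.3115 | 7.7 | 0.0354 | 2.16 | 58% |

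The r that would mimic the whole 10-point design effect is 0.10 / 0.765 = 13.1%.

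**Step 4. Budgeted interviewer time.** 12 assistants × 10 days = 120 person-days. For 1,736 women that is 1,736 / 120 = 14.5 women per person-day. The study profile shows periods of 4 and 10 months, and each woman's endpoint is up to four weeks after the pregnancy ends (4.4.6). The budgeted days could hardly support a running log of revisit dates, so visit data would probably come from continuing files or cards. That makes it important to say which ones.

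**The case against.** A reader might infer that the CHW and Health Assistant team records all primary outcomes in the intervention arm, so that ascertainment does differ by arm. The documents do not establish this:

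- The delivery line names no actor. The same part of Annex 15 also refers to a researcher: "the researcher will want to know whether the child is still alive just at one month". Annex 6 is administered by trained research assistants in sub study two (4.3.6).
- The main text and the budget point to research assistants, without distinguishing the arms.
- The Health Assistant line concerns the prenatal woman. It fits the antenatal file used to tailor counselling and need not reach delivery or newborn data. CHW recording of newborn practices is an inference.
- Annex 15 i) contains eligibility and consent steps that both arms need, so it is not plainly confined to the intervention arm. Section 4.4.6 collects phone contacts from all recruited women for follow-up.
- Section 1.5.3 expects a Health Assistant at each health centre II and III, so the cadre may exist in control centres. What is particular to the intervention arm is the designated team.
- The self-report argument does not carry over to clinic attendances.
- The misrecording rates are assumptions, and 4.4.10 does not say that the test will allow for clustering.

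All of this stands, and it rules out presenting differential ascertainment as settled fact. It does not remove the contradiction. Outcome-recording instructions sit inside the intervention package, no counterpart is written for control centres, and nothing says that the main text prevails.

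**Conclusion.** The point holds as a contradiction with a conditional consequence. The protocol does not settle who ascertains the primary outcomes, and one of its two accounts would put recording with the unblinded intervention team in one arm only. If that account is followed, the error could be differential, chiefly for place of delivery and newborn practices and less for ANC attendance.

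The size can only be illustrated: 1.5 to 7.7 spurious points and a false-positive chance of about 7% to 58% for misrecording of 2% to 10%. This rests on no true effect, 23.5% in both arms, 788 analysed per arm and a test that uses D = 2.5. If the research-assistant account is followed in both arms, this arm-specific mechanism does not arise, although assessor masking would still be unstated. The protocol should be corrected before enrolment. The matter concerns trial conduct and is not a detail that a statistical analysis plan would normally supply.

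**What to change.** Reconcile 4.4.9 and 4.4.10 with Annex 15 by stating one procedure for both arms:

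1. Primary outcomes come only from the planned research assistants, with the same tool and the same follow-up window in both arms.
2. Visit dates and place of delivery are taken from ANC cards and maternity registers where these exist.
3. The files kept by CHWs and Health Assistants are process monitoring and are not used for outcomes. The outcome lines in Annex 15 i) are moved to the research assistants' procedure or labelled accordingly.
4. Where feasible, assistants rotate across arms.

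No new cadre of assessor is needed. The cost is more than wording, however. Follow-up in both arms means more travel and scheduling for the assistants, possibly beyond the 120 person-days budgeted. Rotation is harder because the arms are placed at opposite extremes of the districts, so it should remain a preference and not a requirement.

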## 4.3.7 Study variables

- Maternal homecare practices
  - Nutritional requirements
  - Initiation of ANC attendance
  - Birth preparations
  - Exertion during pregnancy
- Neonatal home care practices
- Care during delivery
  - Care for the cord (cutting and cleaning)
  - Warmth for the newborn
  - Initiation of breast feeding
  - Provision of pre-lacteal feeds
- Harmful maternal and newborn practices
- Healthy maternal and newborn practices

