## 4.4.1 Introduction

The ultimate intervention will be based on data obtained from the two formative surveys and; based on our own knowledge about the context of Masindi and Kiryandongo and the subject of maternal and newborn care. The first study with health workers will inform the design of re-orienting health services at the antenatal clinic, while the community survey will form a basis for the appropriate educational messages to be delivered at the ANC clinics.

Primary outcomes of interest in this study are timely return ANC visits, completed four ANC visits, institutional delivery, and neonatal homecare practices. Secondary outcomes are post intervention community and health workers perceptions about the educational intervention offered by CHWs at the primary care facility.

The educational intervention will consist of **i)** a promotional team of community health workers supervised by a health assistant providing educational interventions at the primary care facility and; **ii)** the promotional team at the health centre using mobile phone reminders through Community Health Workers to pregnant women at the households.

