### 4.4.7 Study variables

## Independent/factor:

(i) Routine ANC care available in the health facilities (standard care);

(ii) *Promotional team* giving additional education care to pregnant women with periodic mobile phone reminders.

*Dependent/outcome variables*

1. Timely return ANC visits (return within seven days of the scheduled appointment date)
2. Completion of the four recommended ANC visits
3. Institutional deliveries
4. Newborn care practices:
5. Provision of warmth to the newborn
6. Initiation of breastfeeding within one hour of birth
7. Care for the cord
8. Immunization for the newborn-Polio 0 & 1; BCG within the neonatal period

We will, at the end of the study, assess perceptions of individual women who have participated in this intervention towards the integrated package by administering the tool described by Howie and others ([Howie J, Heaney D et al. 1998](#_ENREF_42)) elaborated in annex 15 (the Patient-Enablement Initiative (PEI).

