**E. Warmth**

1. At what stage after delivery was the newborn dried up

1. Immediately before the placenta was delivered
2. Immediately after delivery of the placenta
3. After the mother was cleaned and wrapped
4. After the whole process of the delivery was completed
5. Not dried, just wrapped

2 .At what stage was the newborn wrapped up in a warm cloth

1. Immediately before the placenta was delivered
2. Immediately after the placenta was delivered
3. Long after the delivery was competed

3. What was the timing of the first bath after delivery?

1. Immediately after delivery;
2. Not immediately but within 6 hours;
3. 7-23 hours after;
4. Second day after delivery or later

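### Annex 6, the questionnaire named for the newborn outcomes, has no item on when breastfeeding began or on pre-lacteal feeds, so as printed it gives no data on one of the four newborn-care primary components

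*Protocol*

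**What the plan says.** Section 4.4.1 sets the status of the outcome: "Primary outcomes of interest in this study are timely return ANC visits, completed four ANC visits, institutional delivery, and neonatal homecare practices". Section 4.4.7 divides newborn care practices into four components: warmth, breastfeeding, cord care and immunisation. The breastfeeding component is defined as "Initiation of breastfeeding within one hour of birth", and section 4.4.10 repeats it among the outcomes to be analysed. The protocol's operational definition of homecare practices also includes initiation of breastfeeding.

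For measurement, Annex 15, SOP i) states: "Assess for the different practices outlined annex 6 will be used to assess the following outcomes". The list that follows begins "Place of delivery, Cutting of the cord, care for the cord, initiation of breast feeding, provision of pre-lacteal feeds".

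Annex 6 is headed as the structured interview for lactating women in sub-study two, and section 4.3.6 names it for that survey. The sub-study two variables in section 4.3.7 include initiation of breastfeeding and "Provision of pre-lacteal feeds". One printed form is therefore meant to supply the same two variables to both studies.

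**The concern.** The protocol defines an outcome, names the form that will capture it and prints the form, and the form has no question for it. This is a contradiction inside the document, not a detail left to a statistical analysis plan.

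In the trial, a listed component of a primary outcome would have no data in either arm. Time to first feed has to be asked of the mother, and follow-up ends four weeks after the pregnancy ends, so an omission found at analysis would be hard to repair. The education package also covers pre-lacteal feeding and colostrum, so a taught behaviour would go unmeasured.

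In sub-study two, section 4.4.1 makes the community survey the basis for the educational messages. The survey could not report how common early breastfeeding or pre-lacteal feeding is, nor relate either to mothers' characteristics as section 4.3.8 plans.

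**Working it through.** No arithmetic applies. The check sets each newborn-care component in section 4.4.7, and the one further feeding outcome in the SOP, against every item of Annex 6.

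| Outcome | Where listed | Item in Annex 6 |
|---|---|---|
| Warmth | 4.4.7 | Section E: drying, wrapping, first bath |
| Breastfeeding within one hour | 4.4.7; SOP i) and 4.3.7 as initiation | None |
| Cord care | 4.4.7, SOP i), 4.3.7 | Section D: cutting, tying, substance applied |
| Immunisation (Polio 0, Polio 1, BCG) | 4.4.7 | Section H: one yes/no item for each |
| Pre-lacteal feeds | SOP i), 4.3.7; not in 4.4.7 | None |

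Three of the four section 4.4.7 components have items. Breastfeeding is the exception.

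The remaining sections of Annex 6 do not fill the gap. Section A covers demographics, B the last pregnancy, C the delivery, F assessment of the newborn, and G postnatal visits. Feeding appears in two places only: extra or more frequent feeds as answer options for special care of a premature baby (section F), and failure to feed as a way the mother noticed illness (section H). Neither gives the time or the content of the first feed. The form does ask for timing elsewhere ("What was the timing of the first bath after delivery"), so a timed question suits its style. Section letters run from A to H without a break, so a lost section is an unlikely explanation.

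Related questions exist in other tools, but they are put to other people:

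- Annex 1 asks health workers when breastfeeding should start. It is a knowledge item.
- Annex 7 asks birth attendants and elderly caregivers when they start to feed a baby and what they give when there is no breast milk. It describes usual practice.
- Annex 8 puts open questions to 30 mothers in in-depth interviews and has no specific item on first feeding.

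None of these records what happened to an individual trial participant's baby.

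**The case against.** A reader might infer that breastfeeding within one hour cannot be measured in this trial and will be missing for every woman. The documents do not support that. Section 4.4.9 says the trial will use semi-structured questionnaires, which are not appended and may contain the item. The SOP itself tells staff to assess initiation of breastfeeding. Section 4.3.4 places the birth attendant and caregiver interviews before the survey so that new themes can be added to the mothers' questionnaire, and Annex 7 does raise first feeding. The tools are also pre-tested, twice in sub-study two and for one day in the trial.

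This limits the claim to Annex 6 as printed, but it does not remove the mismatch. None of these provisions supplies an item, and a pre-specified outcome should not depend on a theme happening to emerge or on a pre-test happening to catch an omission. If the trial questionnaire has the question, the SOP points to the wrong form.

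Two further limits stand. A reader of the SOP list might take pre-lacteal feeding to be a primary component as well, but section 4.4.7 does not list it. And sub-study two is not left without information on feeding: Annexes 7 and 8 can still inform the messages qualitatively. What is lost is the quantitative prevalence among mothers.

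**Conclusion.** The concern holds for Annex 6 as printed. It contains no item on time of first breastfeed and none on pre-lacteal feeds, although the SOP names it for both. One of the four newborn-care components under a primary outcome would have no data in either arm, and sub-study two could quantify neither practice.

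The planned totals are 1,736 women in the trial and 823 mothers in sub-study two. Both are recruitment targets that already include a 10% allowance for loss or non-response, so they are upper limits on the number of interviews affected.

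The conclusion assumes that the printed annex is the complete form and that it is used unamended. The sample size rests on institutional delivery, which Annex 6 does record, so power for that outcome is untouched. The point should be corrected before fieldwork, but it does not threaten the trial as a whole.

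**What to change.** Before pre-testing, add two items to Annex 6 and to the trial outcome questionnaire:

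- Time from birth to first breastfeed, with answer categories that separate within one hour from later and allow for a baby not yet breastfed.
- Whether anything was given before the first breastfeed and, if so, what.

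If another tool already records these, name it in Annex 15, SOP i) in place of Annex 6, and append it. Sub-study two would still need both items in its own form.

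The cost is two short questions and the matching data-entry fields, with no change to design, sample size or visits.
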